**Screening**							
Informed consent	✓						
Medical consultation	✓						
Anthropometry	✓		✓		✓	✓	✓
Pain VAS	✓		✓		✓	✓	✓
Fatigue VAS	✓		✓		✓	✓	✓
MINI	✓						
MCM/Randomization	✓						
**Questionnaires**							
PGIC	✓		✓		✓	✓	✓
APAQ	✓		✓		✓	✓	✓
FSS	✓		✓		✓	✓	✓
HADS	✓		✓		✓	✓	✓
PCS	✓		✓		✓	✓	✓
Pittsburgh	✓		✓		✓	✓	✓
**Accelerometry**	✓		✓		✓	✓	✓
**Cardiorespiratory capacities**							
ECG	✓		✓		✓		
RFE	✓		✓		✓		
VO_2_max	✓		✓		✓		
**Muscular capacities**							
Isometric strength^*^	✓		✓		✓		
Dynamic strength^$^	✓		✓		✓		
Endurance strength^$^	✓		✓		✓		
**EXPLORATION OF THE ANS**							
Baroreflex	✓		✓		✓		
**EXERCISE SESSIONS**							
Pain and fatigue tolerance (VAS)		✓		✓			
PA adhesion			✓		✓	✓	✓
**Therapeutic education**							
Educational diagnosis	✓				✓		
TPE sessions		✓					
**Health expenditure reporting**						✓	✓

*VAS, visual analog scale; MINI, mini international neuropsychiatric interview; MCM, multidisciplinary consulting meeting; PGIC, patient global impression of change; APAQ, adult physical activity questionnaire; FSS, fatigue severity scale; HADS, hospital anxiety and depression scale; PCS, pain catastrophizing scale; ECG, electrocardiogram; RFE, respiratory functional exploration; VO_2_max, maximum oxygen consumption; ANS, autonomic nervous system; PA, physical activity; TPE, therapeutic patient education*.

* *arms and legs*.

$ *legs*.

### Sample Size

Population size is calculated on an expected difference of 20% of the level of MVPA (≥3 METs for metabolic equivalent tasks). Estimating that at baseline, patients are at 3.9 MET-h/week with a standard deviation between 2 and 4 (40), for an alpha risk of 5% and a potency set at 90%, we need to include 150 patients per group; adding an expected dropout rate of 10%, it is necessary to include 165 patients per group to meet the main goal, which means a total of 330 patients.

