### Statistical Analysis

The included population will first be described globally and in groups (test or control), the comparability of the groups will be verified. For quantitative variables, Student's *T*-tests or rank tests (in case of non-normal distribution) will be implemented. The normality of the variables will be checked beforehand with a Shapiro-Wilk test. For qualitative variables, chi-square or Fisher-exact tests (if theoretical numbers are insufficient) will be used. The results will be considered significant at the 5% threshold. The analysis will be carried out in intent-to-treat. An analysis of the main endpoint will be done per protocol. Patients who do not perform 85% of the exercises will be excluded from per-protocol statistical analysis. In addition, we will lead a qualitative study through semistructured individual interviews conducted by a sport and health sociologist. Thirty patients will be recruited in each of the two groups (41, 42). A full transcript will be followed by a thematic and comparative analysis of the cross-data content.

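### The claimed 90% power with 150 patients per group holds only at the bottom of the protocol's own SD range of 2 to 4; power is about 61% at SD 3 and 39% at SD 4

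*Protocol article*

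**What the plan says.** The Sample Size section of the protocol article sets the target effect: "Population size is calculated on an expected difference of 20% of the level of MVPA". The reference values follow: "Estimating that at baseline, patients are at 3.9 MET-h/week with a standard deviation between 2 and 4 (40", where 40 is a citation. Alpha is 5% and power 90%. The result is stated without qualification: "we need to include 150 patients per group; adding an expected dropout rate of 10%, it is necessary to include 165 patients per group", for a total of 330. The section does not say which SD between 2 and 4 produced the 150, or whether the test is one- or two-sided.

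The Statistical Analysis section plans Student's t-tests for quantitative variables, with the alternative that "rank tests (in case of non-normal distribution) will be implemented". On significance it says only: "The results will be considered significant at the 5% threshold". It describes no adjustment for the baseline value.

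**The concern.** Going from SD 2 to SD 4 multiplies the variance by four, and the required sample size with it. One sample size cannot deliver 90% power across such a range, yet the text sets the range beside a single sample size and a single power as though it could. A reader cannot tell that the favourable end was used.

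The power claim affects how the result will be read. A design with 90% power misses a true 20% difference one time in ten. If the SD is 3, this design misses it about four times in ten; if the SD is 4, about six times in ten. A non-significant result set against a quoted 90% power would then look like much stronger evidence against the supervised programme than it is.

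The SD is also a baseline figure used for a comparison at 1 year. That is common in planning, but the article does not say why the spread should stay the same.

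**Working it through.** **Inputs, all from Sample Size except the last two**
- Difference: 0.20 × 3.9 = 0.78 MET-h/week
- SD: 2 to 4
- Alpha 5%, power 90%
- 150 per group before dropout, 165 after, equal groups
- Two-sided test (assumed; sidedness is not stated)
- Unadjusted comparison of two means (Statistical Analysis)

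**Reproducing the plan's figure**

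n per group = 2 × (1.960 + 1.282)² × SD² / 0.78² = 34.54 × SD²

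Setting n = 150 gives SD = √(150 / 34.54) ≈ 2.08. So 150 can be reproduced, but only with an SD almost at the lower limit. At exactly SD 2 the formula gives 139.

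**Power across the stated range**

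Power at 150 per group = Φ(0.78 / (SD × √(2/150)) − 1.960), with √(2/150) = 0.1155. For SD 3: 0.78 / 0.3464 = 2.252, and Φ(0.292) = 0.615.

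| SD | n per group for 90% power | Power at 150 (normal approximation) | Power at 150 (noncentral t) |
|---|---|---|---|
| 2 | 139 | 92.2% | 92.0% |
| 2.08 | 150 | 90.1% | 89.9% |
| 2.5 | 216 | 77.1% | 76.8% |
| 3 | 311 | 61.5% | 61.2% |
| 3.5 | 424 | 48.8% | 48.6% |
| 4 | 553 | 39.3% | 39.1% |

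Power falls below 80% once the SD exceeds about 2.41.

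**Difference detectable with 90% power at 150 per group**

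3.242 × SD × √(2/150) gives 0.75 MET-h/week (19% of 3.9) at SD 2, 1.12 (29%) at SD 3 and 1.50 (38%) at SD 4.

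**Other readings of the calculation**
- One-sided 5% test: 90% power holds up to SD 2.31, then 73% at SD 3 and 52% at SD 4.
- Log scale with a ratio of 1.2: about 148, 294 and 454 per group at SD 2, 3 and 4.
- Rank test with efficiency 0.955: 139 / 0.955 ≈ 146 at SD 2.
- A 20-percentage-point difference in proportions, with control rates of 30% to 50% (assumed): 124 to 140 per group, so this does not give 150.

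None of these supports 90% power at SD 3 or above.

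**Baseline adjustment**

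The residual SD is SD × √(1 − r²), where r is the correlation between baseline and 1 year. The article gives no value of r, so those below are assumptions.

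| r | Power at SD 3 | Power at SD 4 |
|---|---|---|
| 0.3 | 66% | 42% |
| 0.5 | 74% | 50% |
| 0.7 | 88% | 66% |
| 0.85 | 99% | 89% |

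**Dropout**

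150 × 1.10 = 165, but 165 × 0.90 = 148.5. Keeping 150 evaluable needs 150 / 0.90 = 166.7, that is 167 per group. At 148.5 per group, power is 92%, 61% and 39% at SD 2, 3 and 4, so this has almost no effect.

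**The case against.** The strongest reply is that 150 per group does give 90% power at an SD inside the stated range, so the fault is an undisclosed assumption and not a wrong sum. A condensed article might leave the chosen SD to the full protocol. That would be fair if the article named no SD. It prints a range and an unqualified power claim side by side, and the one contradicts the other over most of the range.

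The range may also summarise different groups in the cited source, so its values need not be equally plausible. Eligibility requires less than 150 minutes of regular activity a week, which Assessment Measures equates to 7.5 MET-h/week. If baseline values all lay between 0 and 7.5 with mean 3.9, the SD could not exceed √(3.9 × 3.6) = 3.75, and an even spread over that interval would give 7.5 / √12 ≈ 2.17, with power of about 88%. This lessens the weight on the SD 4 figure. It does not establish 90%: eligibility may not match accelerometry, and nothing caps the spread at 1 year.

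Two further points stand. The SD of about 2.08 is solved backwards from 150. SD 2 with a rank test (146) or on the log scale (148) could also have been rounded to 150, so only the sponsor can say what was used. And Assessment Measures also expresses the primary outcome as reaching 7.5 MET-h/week. If that threshold is what will be tested, neither the article's power nor the figures here apply. The article nonetheless sizes the trial on a mean and an SD, and that is the claim checked here.

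**Conclusion.** The concern holds. With 150 per group and a difference of 0.78 MET-h/week, 90% power requires an SD no larger than about 2.08. Over the protocol's own range, power runs from 92% down to 39%, and it is below 80% for every SD above about 2.41, which is roughly four-fifths of the range: (4 − 2.41) / 2 ≈ 0.80.

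This rests on three assumptions: a two-sided test, the 20% taken relative to 3.9, and the baseline SD carried to 1 year. A one-sided test does not change the conclusion. The dropout slip is real but negligible, at 1.5 patients per group.

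**What to change.** Keep 330 patients and rewrite the Sample Size paragraph:

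- State the single SD, the sidedness and the test used. The sponsor should confirm the SD; about 2.1 is only what the 150 implies.
- Give power across the stated range: 92% at SD 2, 61% at SD 3 and 39% at SD 4.
- Give the difference detectable with 90% power: 1.12 MET-h/week (29%) at SD 3 and 1.50 (38%) at SD 4.
- Correct the expected evaluable number to 148 per group. The power figures above are unchanged to the nearest point.
- If a baseline-adjusted primary analysis is adopted, report its power over a range of baseline-to-1-year correlations. At a correlation of 0.7, power would be about 88% at SD 3 but 66% at SD 4.

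The cost is a reworded paragraph and a less favourable power statement. Rewording does not restore the power. Of the changes considered here that add no patients, only the baseline-adjusted analysis could recover part of it, and how much depends on a correlation that the article does not give.

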## Abstract

**Introduction:** Fibromyalgia (FM) is characterized by multiple symptoms including pain, fatigue, and sleep disorders, altering patient's quality of life. In the absence of effective pharmacological therapy, the last European guidelines recommend a multidisciplinary management based on exercise and education. Thus, our main objective was to measure the effectiveness of a healthcare organization offering a specific program of adapted physical activity combined with a therapeutic education program for FM patients.

**Methods and Analysis:** The From Intent To Move (FIMOUV) study will recruit 330 FM patients randomized into two groups: test and control. The test group will benefit from a 1-month mixed exercise training program supervised at the hospital, followed by 2 months in a community-based relay in a health-sport structure. In addition, each of the two groups will benefit from therapeutic patient education sessions. The main endpoint is the measurement of the level of physical activity by accelerometry at 1 year. The secondary endpoints concern adherence to the practice of physical activity, impact on lifestyle, state of health, and physical capacity, as well as an estimate of the budgetary impact of this management strategy.

**Discussion:** This interventional research will allow us to assess the evolution of behaviors in physical activity after an FM syndrome management based solely on patient education or based on a supervised and adapted practice of physical activity associated with this same therapeutic education program. It seems to be the first study evaluating the impact of its intervention on objective data for measuring physical activity and sedentary behavior *via* accelerometry among FM patients.

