### Assessment Measures

The primary outcome of interest will be the long-term therapeutic adherence of FM patients evaluated from an objective measure of physical activity (mean measured from 7 days of accelerometry; Actigraph GT3x, Pensacola, Florida, USA) 1 year after the setup of the organization of care offering initiation and support of APA during 3 months. This sustainability will result in a level of physical activity ≥7.5 MET-h/week at 1 year, corresponding to 150 min of moderate intensity physical activity per week, which is consistent with WHO recommendations.

The secondary objectives will evaluate the impact on the lifestyle (average time of physical activity and sedentary behavior, measured by accelerometry during 7 days), health status, fatigue, sleep, psychic distress, muscular strength and endurance, physical capacity, tolerance to pain and fatigue during training sessions, membership to physical activity, evaluation of the differential cost-effectiveness ratio, and finally an estimate of the budgetary impact of this care strategy.

Details and timetable are shown in Table 2.

**Table 2 T2:** Assessment measures timetable.

	**Inclusion visit V1**	**Intervention 1st month**	**Post-intervention visit V2**	**Intervention 2nd and 3rd months**	**Post-intervention visit V3**	**Intermediate visit V4**	**Final visit V5**

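### The 10% dropout allowance is added to 150 rather than divided out, so 165 per group leaves about 148 evaluable, just under the plan's own 150 (minor)

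*Protocol article*

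**What the plan says.** The Sample Size section of the protocol article builds the number in two steps. First, for a 5% alpha risk and 90% power, it concludes "we need to include 150 patients per group". Second, it allows for patients who leave: "adding an expected dropout rate of 10%, it is necessary to include 165 patients per group to meet the main goal". The section then doubles 165 to a total of 330, and the Abstract repeats that total: the study "will recruit 330 FM patients randomized into two groups".

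The inputs to the first step are a difference described as "Population size is calculated on an expected difference of 20% of the level of MVPA" and the statement that at baseline "patients are at 3.9 MET-h/week with a standard deviation between 2 and 4". The article does not say which standard deviation in that range was used, or whether the test is one- or two-sided. It gives no other dropout figure and no inflation formula.

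**The concern.** Patients drop out of those who were included. If 10% of the included patients are lost, the number included must be divided by 0.90 to leave the required number; multiplying the required number by 1.10 falls slightly short. The article presents 165 as the number necessary to reach the main goal under a 10% dropout rate, and on its own inputs it is not quite that number.

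What is at stake is the accuracy of a figure on which the trial relies. The primary measure is a 7-day accelerometer recording at 1 year, so a patient who has left before then provides no such recording. The number still evaluable at 1 year is therefore the one that should match the 150.

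**Working it through.** **Inputs** (protocol article, Sample Size): 150 required per group; 10% expected dropout; 165 included per group; 330 in total; alpha 5%; power 90%.

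**1. Reproduce the plan's figure.** Required number x (1 + dropout) = 150 x 1.10 = 165, and 2 x 165 = 330. This matches exactly, so the allowance was added on top of 150.

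**2. Apply the stated dropout rate to the stated enrolment.**
- Per group: 165 x (1 - 0.10) = 148.5, which is 1.5 below 150.
- In total: 330 x 0.90 = 297, against 2 x 150 = 300.

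**3. Dropout rate that 165 can absorb.** (165 - 150)/165 = 15/165 = 9.1%.

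**4. Enrolment that keeps 150 after a 10% loss.** 150/(1 - 0.10) = 166.7, rounded up to 167 per group, or 334 in total. The difference from the plan is 2 per group and 4 in total (4/330 = 1.2%).

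**5. Effect on power, if 150 is exactly the size for 90%.** No standard deviation is needed for this step. In the normal approximation with a two-sided 5% test, the standardised effect at 150 per group must equal 1.960 + 1.282 = 3.242. It scales with the square root of the number evaluable:

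| Evaluable per group | Standardised effect | Minus 1.960 | Power |
|---|---|---|---|
| 150 | 3.242 | 1.282 | 90.0% |
| 148.5 | 3.242 x √(148.5/150) = 3.225 | 1.265 | 89.7% |
| 148 | 3.242 x √(148/150) = 3.220 | 1.260 | 89.6% |

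The loss is 0.3 to 0.4 percentage points.

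**6. Can the basis of 150 be recovered?** Use n per group = 2 x (3.242)² x (SD/difference)², rounded up, and two-sided 5%. The first four rows assume that the 20% applies to the baseline mean, so the difference is 0.20 x 3.9 = 0.78. The last row takes 20% of the 7.5 MET-h/week threshold in Assessment Measures, 0.20 x 7.5 = 1.5; the article does not state this as the base.

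| Difference | SD | n per group |
|---|---|---|
| 0.78 | 2 | 139 |
| 0.78 | 2.08 | 150 |
| 0.78 | 3 | 311 |
| 0.78 | 4 | 553 |
| 1.5 | 4 | 150 |

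At least two combinations give 150, and a one-sided test would add another (difference 0.78, SD about 2.3). The article does not settle which was used. At a difference of 0.78 and SD 2, 148 evaluable per group gives 91.85% power by the normal approximation (91.7% by the t-test), above 90%. At the same difference with SD 3 or 4, power at 148 is 60.9% or 38.9%, and going to 167 raises it only to 66.1% or 42.9%.

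**The case against.** The strongest reply is that the gap is negligible. It is 1.5 evaluable patients per group, and the expected 10% is itself a round planning figure. A reviewer working to a tolerance of a couple of patients would accept 165. This stands: no design or analysis decision changes, and the point should be rated no higher than a wording correction.

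A second reply is that the sentence speaks of adding the rate, so 165 is simply 150 plus 10% of 150 and contradicts nothing. This stands only in part. The quantity is called a dropout rate and is turned into a number to include, so the natural base is the patients included. If 10% of completers was meant, the dropout allowed for is 9.1% of enrolment, and the sentence should say so.

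A third reply is that the analysis is by intention to treat, so everyone counts. But the plan's own inflation step treats dropouts as lost from the 150, and a patient who has left yields no 1-year recording.

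A reader might infer from the shortfall that the trial fails to deliver its stated 90% power. The document does not support that. The standard deviation behind 150 is not given. At the lower end of the stated range with a difference of 0.78, power stays above 90% with 148 evaluable. At the middle or upper end it is far below 90% whether 148, 150 or 167 are evaluable. The 1.5 patients decide the matter only if 150 is almost exactly the 90% size. A reader might likewise take an SD of 2.08 as the one value behind 150. It is not: a difference of 1.5 with SD 4 also gives 150.

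**Conclusion.** The point holds as a minor arithmetic correction. On the article's own inputs, 165 per group leaves about 148 after a 10% loss, not 150, and absorbs only 9.1% dropout; exact inflation gives 167 per group and 334 in total. This rests on one assumption, that the dropout rate is a share of the patients included. The power cost of 0.3 to 0.4 points depends on a second, that 150 is exactly the size for 90%. What is established is a small shortfall against the stated 150, not a failure of power. The unspecified standard deviation is a larger uncertainty, but it is a separate matter and does not affect the dropout arithmetic.

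**What to change.** Keep 330 and correct the sentence in Sample Size in one of two ways:

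- state that 10% dropout from 165 leaves about 148 evaluable per group (297 in total), with power marginally below the nominal 90%, by about 0.3 to 0.4 points if 150 is the exact size for 90%; or
- state that 330 allows for about 9% dropout.

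Either costs one sentence and no extra recruitment; the only loss is a marginally less favourable statement. If the sponsor prefers to protect 150 under a full 10% loss, the figure becomes 150/0.90 = 167 per group, 334 in total. That costs 4 more patients and a matching change to the total in the Abstract. The corrected sentence should not quote a standard deviation reconstructed from 150, because the article does not state which one was used.

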### Randomization and Data Collection

Randomization and data collection will be centralized *via* the EnnoV Clinical platform (electronical randomization, Paris, France) and filled in by the referral doctor and the nurse/APA teacher duo. Only investigators and technicians of the study have access to these data.

Patients will be randomized after a multidisciplinary consulting meeting carried out in the presence of the investigators of the study, the referring doctor and, if necessary, with their general practitioner, before the program starts. This meeting aims to decide about the optimal care for the patient. It will be decided if the patient can follow an exercise training. In case of contraindication, the patient will not be randomized into the study.

### Statistical Analysis

The included population will first be described globally and in groups (test or control), the comparability of the groups will be verified. For quantitative variables, Student's *T*-tests or rank tests (in case of non-normal distribution) will be implemented. The normality of the variables will be checked beforehand with a Shapiro-Wilk test. For qualitative variables, chi-square or Fisher-exact tests (if theoretical numbers are insufficient) will be used. The results will be considered significant at the 5% threshold. The analysis will be carried out in intent-to-treat. An analysis of the main endpoint will be done per protocol. Patients who do not perform 85% of the exercises will be excluded from per-protocol statistical analysis. In addition, we will lead a qualitative study through semistructured individual interviews conducted by a sport and health sociologist. Thirty patients will be recruited in each of the two groups (41, 42). A full transcript will be followed by a thematic and comparative analysis of the cross-data content.

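### Free improvement: the named between-group tests are all unadjusted, although V1 accelerometry is scheduled for every patient and could serve as covariate for the 1-year comparison

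*Protocol article*

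**What the plan says.** Protocol article, Statistical Analysis: the population is described overall and by group, and "the comparability of the groups will be verified". Tests then follow by type of variable. Quantitative variables get Student's t-tests, or "rank tests (in case of non-normal distribution) will be implemented", with normality judged by Shapiro-Wilk. Qualitative variables get chi-square or Fisher exact tests. The analysis is by intention to treat, with a per-protocol analysis of the main endpoint. The article mentions no covariate, ANCOVA, regression model, mixed model or change score.

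The main endpoint is 7-day accelerometry at 1 year (Abstract; Introduction; Assessment Measures). Assessment Measures also expresses it as reaching at least 7.5 MET-h/week.

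Table 2: the row "Accelerometry" is ticked at V1, V2, V3, V4 and V5.

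Sample Size: the calculation rests on an "expected difference of 20% of the level of MVPA", with the assumption that "at baseline, patients are at 3.9 MET-h/week with a standard deviation between 2 and 4", "for an alpha risk of 5% and a potency set at 90"%. It gives 150 per group before dropout and uses no baseline correlation.

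**The concern.** The V1 recording is the same measure as the outcome, taken with the same method in the same patient. If it correlates with the V5 value, putting it in the model removes that part of the between-patient variance from the treatment comparison, at the cost of one degree of freedom. It also removes the linear effect of any chance difference in starting activity. Verifying comparability does neither: it describes an imbalance but leaves the estimate and its standard error unchanged.

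At stake is precision. Over much of the SD range that the protocol itself gives, 150 per group has well under 90% power for the stated difference, so an efficiency gain from data already scheduled is worth taking.

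**Working it through.** **Inputs from Sample Size:** mean 3.9 MET-h/week, difference 20%, SD 2 to 4, alpha 5%, power 90%, 150 per group. Sidedness is not stated; two-sided is assumed. The difference is read as 0.20 × 3.9 = 0.78 MET-h/week.

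**Input not in the documents:** the V1–V5 correlation ρ. Assumed values are 0.3, 0.5 and 0.7.

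**The plan's own figure.** With n per group = 2 × SD² × (1.96 + 1.2816)² / 0.78²:

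- SD 2: 138.2, so 139
- SD 3: 310.9, so 311
- SD 4: 552.7, so 553

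The stated 150 corresponds to SD = 0.78 × √(150/2) / 3.2415 = 2.08, close to the lower end of the range. Under this reading 150 is not reproduced at SD 2, 3 or 4. That is a sample-size question in its own right; here it only shows where the unadjusted test starts from.

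**Effect of adjustment.** ANCOVA on V1 has residual SD = SD × √(1 − ρ²). The equivalent unadjusted sample is 150 / (1 − ρ²) per group:

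- ρ 0.3: 150 / 0.91 = 165
- ρ 0.5: 150 / 0.75 = 200
- ρ 0.7: 150 / 0.51 = 294

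**Power with 150 per group**, difference 0.78, two-sided 5%, noncentral t:

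| SD | unadjusted | ρ 0.3 | ρ 0.5 | ρ 0.7 |
|---|---|---|---|---|
| 2 | 92% | 94% | 97% | >99% |
| 3 | 61% | 65% | 74% | 88% |
| 4 | 39% | 42% | 49% | 65% |

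The normal approximation agrees within one percentage point.

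**Sample size per group for 90% power** (normal approximation):

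| SD | unadjusted | ρ 0.3 | ρ 0.5 | ρ 0.7 |
|---|---|---|---|---|
| 2 | 139 | 126 | 104 | 71 |
| 3 | 311 | 283 | 234 | 159 |
| 4 | 553 | 503 | 415 | 282 |

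**Correlation needed for 90% power with 150 per group.** Setting SD × √(1 − ρ²) = 2.08 gives ρ = √(1 − (2.08/SD)²): about 0.72 at SD 3 and 0.85 at SD 4.

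**Why not a change score.** Its variance is 2 × SD² × (1 − ρ), which exceeds SD² when ρ is below 0.5. At SD 3 and ρ 0.3 it needs 436 per group, against 311 unadjusted and 283 with ANCOVA.

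**The case against.** **The article does not tie a test to the primary endpoint.** The tests are listed by variable type directly after the sentence on comparability, so they could be meant for the baseline description, for the outcomes, or for both. This stands. A reader might infer that the protocol explicitly commits the primary endpoint to an unadjusted test; it does not. The application is an inference, supported by the fact that no other between-group test appears.

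**Covariates are usually settled in the analysis plan, which is not shown.** True, and their absence alone would not be a point. Here, however, the article does state a method, and the point is that this method can be improved. If the analysis plan already adjusts for V1, only the wording needs aligning.

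**An unadjusted test is not an error.** This stands. In a randomised trial it is valid, and its type I error already allows for chance imbalance.

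**The gain is assumed.** This also stands. Nothing in the documents shows that activity is stable over a year in these patients. Entry is limited to those under 150 min/week, both arms are coached or advised to change, and the gap is one year; all of these could lower the correlation. At ρ 0.3 the gain is only about 2 to 4 percentage points.

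**The power shortfall belongs to the sample size.** Largely so. At SD 2 the unadjusted test already has about 92%. If the 20% were taken of the 7.5 threshold (1.5 MET-h/week), SD 4 would give exactly 150 per group, though the article does not state that reading.

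**The endpoint may be the threshold.** In that case the chi-square or Fisher branch applies and the t-based figures do not. The fix has to cover both forms.

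**Timing of the V1 recording.** Table 2 puts "MCM/Randomization" in the same V1 column as accelerometry, and a reader might infer that the recording could run past allocation. A shared column does not show the order of procedures within a visit, and the article places randomisation after a multidisciplinary meeting. The documents do not support a finding on this.

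**Conclusion.** The point holds as a free improvement, not as an error. Every between-group test the article names is unadjusted, by inference this includes the 1-year accelerometry comparison, and the best-matched covariate is already scheduled for every patient. Adjusting for it costs one degree of freedom and gains power for any non-trivial correlation.

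For a correlation between 0.3 and 0.7, the gain in power is about 2 to 8 percentage points at SD 2, 4 to 27 at SD 3 and 3 to 26 at SD 4. These figures rest on the assumed correlations, a difference of 0.78 MET-h/week, a two-sided 5% test, 150 per group and the continuous form of the endpoint.

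Two stronger conclusions are not supported. The planned analysis is not invalid or biased. Nor would adjustment rescue the sample size: across the assumed correlations, power stays below 90% at SD 3 and SD 4, so the unfixed SD must be dealt with separately.

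**What to change.** Add to Statistical Analysis:

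- The primary intention-to-treat comparison of V5 MET-h/week is an ANCOVA on arm with V1 MET-h/week as covariate, reported as the adjusted mean difference with its 95% CI.
- Skew is handled by a pre-specified transformation or robust standard errors. A non-negative measure with mean 3.9 and SD up to 4 is likely to be skewed, so this should be settled in advance.
- If reaching 7.5 MET-h/week is the primary form, the comparison is a logistic regression on arm with V1 activity as covariate.

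Do not use a change score as the substitute.

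The cost is a sentence or two in the protocol or analysis plan. No visit, measurement or patient is added.

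### If the primary endpoint is the continuous activity level, a Shapiro-Wilk pre-test chooses between two tests of different hypotheses, and only one matches the mean difference used for sizing

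*Protocol article*

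**What the plan says.** The Statistical Analysis section gives one rule for all quantitative variables: Student's t-tests, or "rank tests (in case of non-normal distribution) will be implemented". It adds that "The normality of the variables will be checked beforehand with a Shapiro-Wilk test". No other test for a quantitative outcome is named, and the main endpoint is not exempted.

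The endpoint is described in two ways:
- As a level. The Abstract says "The main endpoint is the measurement of the level of physical activity by accelerometry at 1 year", and the end of the Introduction describes an average over 7 days of accelerometry.
- As a threshold. Assessment Measures says "This sustainability will result in a level of physical activity ≥7.5 MET-h/week at 1 year". Read as a yes/no outcome, this falls under a different sentence: "For qualitative variables, chi-square or Fisher-exact tests (if theoretical numbers are insufficient) will be used".

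The Sample Size section follows the first description: "Population size is calculated on an expected difference of 20% of the level of MVPA". It assumes that "patients are at 3.9 MET-h/week with a standard deviation between 2 and 4", with 5% alpha, 90% power and 150 patients per group before dropout.

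**The concern.** A t-test compares mean MET-h/week. A rank test asks whether values in one arm tend to exceed values in the other. The two agree when one arm is simply shifted relative to the other, but they can part when the arms differ in shape or spread. A pre-test on the outcome therefore settles after the data are in which question the trial answers, and only one of the two answers is about the quantity the trial was sized on.

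The switch is a real prospect. MVPA cannot be negative, and the stated SD runs from half the mean to slightly more than the mean. A significant rank test could then appear with no difference in mean activity, or the test used could have power quite unlike the planned 90%.

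**Working it through.** **Inputs from the Sample Size section:** mean 3.9, SD 2 to 4, 150 per group. A 20% difference taken relative to 3.9 is 0.20 × 3.9 = 0.78 MET-h/week. A two-sided 5% level is assumed, since sidedness is not stated.

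**1. The plan's own figure.** For two means, n = 2(1.960 + 1.282)² SD² / 0.78² per group:
- SD 2: 139
- SD 2.08: 150
- SD 3: 311
- SD 4: 553

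Neither end of the stated range gives 150; an SD near 2.08 does. The arithmetic fits a comparison of means at the low end of the range. Adding 10% gives 150 × 1.1 = 165, as stated.

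**2. Can the outcome be normal?** A normal curve with mean 3.9 puts this share of patients below zero:
- SD 2: Φ(−3.9/2) = 2.6%
- SD 3: Φ(−3.9/3) = 9.7%
- SD 4: Φ(−3.9/4) = 16.5%

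Exact normality is excluded. Departure is slight at SD 2 and marked at SD 3 to 4.

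**3. How often does the pre-test switch the analysis?** Simulation with 150 per arm and Shapiro-Wilk at an assumed 5% level, applied to each arm (either rejecting) or to the pooled data. The plan gives neither the level nor the unit. All shapes are assumptions.

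| Shape | SD | Switch to rank test |
|---|---|---|
| Gamma or lognormal | 2 to 4 | about 100% |
| Normal censored at 0 | 3 or 4 | 100% |
| Normal censored at 0, no effect | 2 | 28% (either arm) to 59% (pooled) |
| Normal censored at 0, no effect | 2.08 | 43% (either arm) to 80% (pooled) |
| True normal | 2 to 4 | about 10% (either arm), 5% (pooled) |

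**4. Type I error when both arms have the same distribution.** Across these shapes the two-stage rule rejects in 4.3% to 5.5% of trials and the t-test in 4.6% to 5.5%. The pre-test causes no inflation here, and the t-test needs no protection from it.

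**5. Equal means (3.9), unequal spread.**

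| Shape | SDs | t-test rejects | Rank test rejects |
|---|---|---|---|
| Gamma | 2 v 3 | 6% | 32% |
| Gamma | 2 v 4 | 6% | 79% |
| Lognormal | 2 v 3 | 5% | 38% |
| Lognormal | 2 v 4 | 6% | 83% |

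The two-stage rule gives the same figures as the rank test, because the switch always occurs. The reason shows in the medians. A lognormal median is mean/√(1 + SD²/mean²), so it is 3.9/√(1 + 4/15.21) = 3.47 at SD 2 and 3.9/√(1 + 16/15.21) = 2.72 at SD 4. The more variable arm ranks lower although the means are equal.

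**6. Power at a mean difference of 0.78.**

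| Scenario (assumed) | t-test | Rank test |
|---|---|---|
| Gamma, SD 2, 10% of test patients gain 7.8 (0.10 × 7.8 = 0.78) | about 76% | about 32% |
| Gamma, SD 2, mean and SD both 20% higher | 86% | 83% |
| Gamma, SD 3, uniform shift | about 60% | about 81% |
| Lognormal, SD 4, uniform shift | 41% | 91% |

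The direction depends on how the effect is spread over patients.

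**The case against.** - **The endpoint may be binary.** Under the 7.5 MET-h/week threshold the test is chi-square or Fisher, and the pre-test never touches it. This stands, so the point is conditional. The Abstract, the Introduction and the sample size all support the continuous reading.
- **The rule is generic and sits next to the baseline comparison.** It may have been written with baseline tables in mind, and an article can leave the primary model to the SAP. The missing model is not the complaint. The complaint is the rule as printed, which covers every quantitative variable; a SAP would have to override it.
- **A reader might infer that the switch will almost always happen.** The documents state no distribution. Near certainty holds for clearly skewed shapes, but not for a mildly bounded normal near SD 2, where the trial is sized.
- **If the switch were certain, the plan would amount to a fixed rank test.** Correct, and less would then hang on the data. The mismatch with the sizing would remain.
- **A reader might infer lost power or a raised false-positive rate.** Neither holds in general. Type I error is about 5% when the arms share a distribution. The large power loss needs a small group of strong responders, which the documents do not describe; a uniform shift favours the rank test.
- **A reader might infer harm to the cost-effectiveness analysis.** The article does not say that its effect unit is MET-h/week or that it depends on this test. A rank p-value does not prevent reporting a mean difference either.

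**Conclusion.** The point holds in conditional form, with medium confidence. On the continuous reading, the stated rule lets the outcome data choose between a hypothesis about means, which the trial is sized on, and one about ranks, which it is not.

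The harm is a data-driven change of estimand. Its clearest measure is the equal-means case: roughly 30% to 80% rejection by the rank test in skewed data with unequal spread, against about 5% for the t-test. The chance of switching ranges from about 30% to 60% (zero-censored normal, SD 2) to about 100% (clear skew). All of this rests on assumed shapes, a 5% Shapiro-Wilk level and 150 analysed per arm. The effect on power has no fixed sign.

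This is worth correcting but does not invalidate the design. That 150 per group requires an SD near the bottom of the stated range is a separate and larger matter.

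**What to change.** First state whether the primary endpoint is the MVPA level or the 7.5 MET-h/week threshold. If it is the level:
- Remove the normality pre-test for the primary endpoint.
- Name one mean-based analysis in advance: regression of V5 MVPA on arm, adjusted for V1 MVPA, with robust standard errors or a bootstrap confidence interval for the difference in MET-h/week. Table 2 shows accelerometry at both visits, so no new data are needed.
- Report the rank test as a sensitivity analysis, whatever the distribution looks like.

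The cost is a change of wording, and fixing a mean-based test does not alter the required sample size. The downside is real: if the effect is a uniform shift in heavily skewed data, the mean-based test can give up substantial power. In the unadjusted comparisons above this was about 20 points (gamma, SD 3) to 50 points (lognormal, SD 4). The team should accept that knowingly. If it prefers a rank-based primary analysis, it should fix that in advance and size the trial for it.
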